### Data analysis plan

#### Phasic timescale.

***Video recordings and movement synchrony:*** Video recordings of all sharing episodes will be made using three fixed cameras at a frame rate of 25 frames per second. One camera will capture the entire scene of emotional sharing, while the other two will be placed in front of the participants, and their feeds will be connected through split-screen. Before initiating the Motion Energy Analysis (MEA), the split-screen video will allow an independent analysis of each individual to derive objective motion quantification.

The MEA program [28] employs a frame-differencing algorithm, which requires both a static camera-position as well as a stable background setting. Under these conditions, the difference in grayscale pixels between consecutive video frames reflects the bodily movements of participants, which is then quantified into time series of movement. The areas for this kind of quantification can be defined in the program, and we will use a singular region of interest (ROI) encompassing the entire head and upper body of each participant. Based on one ROI per participant, the MEA program will process the video images and generate one CSV file per video containing the time series of raw pixel variations within the designated ROIs. Adjustments for minimal thresholds of movement will be processed in the MEA program according to the criteria suggested by the creator of the program [28]. Following the generation of raw movement data, the rMEA package in R Studio will be employed for further analysis [29].

We will follow the standard pre-processing steps as outlined by Ramseyer and Tschacher (2011) [9] and Tschacher et al. (2018) [30]. Initially, a 0.5-second moving average filter will be applied to smooth the time series, reducing fluctuations caused by signal distortions present in the video data. To account for varying sizes of the ROI, the data will be z-transformed, and extreme outliers will be eliminated. Here, we will use the default threshold provided by the authors of rMEA, thereby excluding extreme values higher than 10 times the standard deviation. Data thus filtered and corrected are then subjected to windowed cross lagged cross-correlation analyses for the quantification of nonverbal synchrony.

Specifically, in each 8-minute dialogue, the motion energies of both participants will be cross-correlated in non-overlapping window segments of 30 seconds. The choice of a 30-second window size (750 frames) is to account for the shorter turn-taking latencies in question-centered discussions, consistent with previous work [30]. Windowed cross lagged cross-correlation of up to 5 seconds of positive and negative time lags will be computed with a step size of 0.1 seconds, achieved by progressively shifting one time series relative to the other [9]. The resulting matrix of cross-correlations will then be transformed using Fisher’s r-to-Z transformation, and their absolute values will be aggregated over the entire 8-minute interval of the dialogue, resulting in a shared global value of nonverbal synchrony for every sharing episode [9].

To ascertain whether the synchrony detected via MEA exceeded what might occur by chance (i.e., pseudosynchrony), we will engage a specific RMEA function designed for generating pseudointeractions through automated surrogate algorithms. This function shuffles the days in the data and calculates all possible motion energy interactions between couples in the dataset. Subsequently, it dissociates the original pairings, followed by the extraction of a predefined amount of unique MEA datasets, each selected just once to avoid duplication.

To test Hypothesis 1, we will examine whether relationship partners show greater synchrony than pseudo-dyads during the emotional sharing tasks. Following recommendations by Helm et al. (2018) [31] and DiGiovanni et al. (2024) [18], we will compute windowed cross-correlations to generate time series of movement synchrony. We will then apply multilevel modeling (MLM) using the *lme4* package in R to compare synchrony scores between real dyads and matched pseudo-dyads, accounting for the nested structure of time windows within dyads. To test Hypothesis 2, we will examine whether co-rumination leads to greater synchrony than natural sharing. Movement synchrony data will be modeled using multilevel models with time windows (Level 1) nested within participants (Level 2) and dyads (Level 3). Experimental condition (co-rumination vs. natural sharing) will be entered as a fixed effect predictor, and dyad ID and participant ID will be modeled as random effects. This approach accounts for both the repeated nature of the synchrony time series and the interdependence between partners in a dyad.

***Cardiovascular measurement and synchrony:*** To collect electrocardiography data, the VU-AMS 7 from Vrije Universiteit Amsterdam will be used. This instrument consists of five non-invasive electrodes placed on the participant’s chest and back. First, by employing automated and visual data cleansing techniques, potentially anomalous R-wave peaks will undergo manual rectification or will be marked as artifacts to ensure the integrity of the inter-beat interval (IBI) series. IBI is defined as the time (in ms) between two consecutive R-peaks in the ECG signal and is automatically scored by the VU-AMS 7 software. Subsequently, the IBI time series will be resampled at a frequency of 10 Hz, and samples will be divided into epochs of 2000 ms with fixed onset and offset to achieve accurate temporal alignment of IBI values within dyads. The selection of a 2000 ms epoch length is based on the minimum time required for reliable estimation of heart rate [32]. For each epoch, the average IBI will be calculated, resulting in a time series of epoch-averaged values for each participant.

For each 2000 ms epoch time series, a second-order polynomial regression will be calculated to remove linear and quadratic trends from the data [33]. To eliminate the autocorrelation properties of the signal, the partial autocorrelation function (PACF) of the detrended IBI time series, (i.e., the residuals after polynomial fitting) will be plotted and analysed. First, the autoregressive integrated moving average (ARIMA) model will be applied to the residuals of the polynomial regression, incorporating one autoregressive term, one moving average term, integrated noise, and the residuals obtained from the analysis as inputs into the cross-correlation calculation.

Finally, the resulting IBI time series will be then further processed in Matlab (The MathWorks, Inc., Natick, MA). Specifically, we will use the Matlab functions ‘parcorr’ for the PACFs, ‘armax’ for ARIMA modelling and ‘xcorr’ (with zero-time lag) for the calculation of the cross-correlations. It is important to note that the two measurement methods used to compute IBI synchrony do not measure the distance at which individual heartbeats occur within the dyad simultaneously. Instead, they assess how the heart rate variability between consecutive 2000 milliseconds epochs co-fluctuate across the entire dyad.

To assess whether cardiovascular synchrony exceeds what would be expected by chance (i.e., pseudosynchrony), we will follow the approach of Feldman et al. (2011) [34] and more recent adaptations by DiGiovanni et al. (2024) [18]. We will first calculate windowed cross-correlations on the interbeat interval (IBI) time series for each dyad during the interaction, using time-lagged windows to account for dynamic shifts in coupling. To test whether the observed synchrony exceeds random coupling, we will generate a surrogate dataset of randomly paired pseudo-dyads, and then use multilevel modeling (MLM) to compare synchrony scores between real and pseudo-dyads. This model will account for the nested structure of time windows within dyads and the repeated nature of physiological data. To test Hypothesis 2, we will use MLM to compare cardiovascular synchrony between the co-rumination and natural sharing conditions, including condition as a fixed effect and random intercepts for dyad and participant where appropriate. This approach allows us to properly model interdependence between partners and repeated time-based observations within each interaction episode.

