#### Chronic timescale.

***Relationship quality and dyadic coping analysis:*** We will employ regression analysis to examine the associations between relationship quality and dyadic coping strategies and movement and cardiovascular synchrony (*Hypothesis 7.1 and 7.2*). Additionally, to analyse whether dyadic coping and relationship quality are associated with mood changes we will add these variables as fixed factors in the linear mixed models built for testing hypothesis 3 on mood change over time (*Hypothesis 7.3*). Linear regression analyses will also be used to assess whether relationship quality and dyadic coping are related to emotional appraisal change (*Hypothesis 7.4*).

To assess whether co-rumination versus natural sharing influences the relationship between higher relationship quality and more constructive dyadic coping and movement and cardiovascular synchrony moderated regression analyses will be used (Hypotheses 8.1 and 8.2). To analyse whether the associations between relationship quality and dyadic coping with mood change are associated with effects of co-rumination versus natural sharing we will extend the linear mixed models used for testing hypothesis 7.3. The full model will consist of a random intercept for participants, fixed factors of assessment time and condition, their interaction, and mood as the dependent variable (*Hypothesis 8.3*). Moderated linear regression analyses will be used to assess whether better relationship quality and dyadic coping are associated with weaker effects of the co-rumination condition versus natural sharing on emotional appraisal change (*Hypothesis 8.4*).

The hypotheses presented in Table 1 and the data analysis techniques utilized constitute the core elements of our research. Additionally, we have identified and measured a range of secondary variables that could potentially influence these associations. Our aim is to incorporate these variables as covariates in the analyses to enhance our understanding of the findings. For all statistical tests α ≤ 0.05 (two-tailed) will be applied. Given the wide range of statistical tests performed, there is a concern regarding multiple comparisons. Therefore, to reduce the likelihood of Type I errors, we will apply the Bonferroni correction to all previously mentioned test results.

***Exploratory analyses summary:*** In our study, we plan to conduct exploratory analyses to investigate interpersonal synchrony in verbal communication:

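### Movement synchrony is built from absolute correlations with a chance floor that depends on movement timing, and the models for H2, H7.1 and H8a state no chance correction

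*Protocol article*

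**What the plan says.** All of this is in the Protocol article, Data analysis plan.

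**Score (Phasic timescale).** Video is taken with "three fixed cameras at a frame rate of 25 frames per second". Then "a 0.5-second moving average filter will be applied to smooth the time series". Scaling follows: "To account for varying sizes of the ROI, the data will be z-transformed, and extreme outliers will be eliminated". Windows do not overlap ("The choice of a 30-second window size (750 frames"), and the lags are set as: "Windowed cross lagged cross-correlation of up to 5 seconds of positive and negative time lags will be computed with a step size of 0.1 seconds". After Fisher's transformation, "their absolute values will be aggregated over the entire 8-minute interval of the dialogue, resulting in a shared global value of nonverbal synchrony".

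**Chance level (Phasic timescale).** The article recognises that some measured synchrony arises by chance and generates pseudo-interactions by re-pairing people. The only model that names pseudo-dyads is the one for Hypothesis 1.

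**Hypothesis 2 (Phasic timescale).** "Experimental condition (co-rumination vs. natural sharing) will be entered as a fixed effect predictor", with random effects for dyad and participant. No pseudo-dyad term, subtraction or standardisation is stated.

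**Hypotheses 7.1 and 8.1 (Chronic timescale; the latter is 8a in Table 1).** "We will employ regression analysis to examine the associations between relationship quality and dyadic coping strategies and movement and cardiovascular synchrony". Hypothesis 8.1 uses moderated regression. Neither states a chance correction.

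**Contrast.** For the cardiac series the article removes autocorrelation with an ARIMA step before cross-correlating. It gives no such step for movement.

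**The concern.** The mean of |Z| is positive even when two people move independently. In a 30-second window, slow or long-lasting movements leave few effectively independent samples, so chance correlations are larger in absolute size. The z-transform takes out scale and the size of the image region. It leaves the temporal structure that sets this floor.

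The co-rumination instruction is meant to change how the supporter converses, so it could also change the timing of head and upper-body movement.

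- **H2:** a shift in the floor between instructions would look like a change in coupling, or would cancel a real one.
- **H8a:** the same applies if such a shift varies with relationship quality or dyadic coping.
- **H7.1:** a couple-level difference in movement style that goes with relationship quality is enough.

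Movement synchrony is a primary phasic outcome, and these hypotheses are listed as confirmatory in Table 1.

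**Working it through.** **Inputs from the article.** 25 frames/s; 0.5 s smoothing; 30 s windows; lags within ±5 s; 150 couples; each couple has two dialogues per condition; two-sided 0.05 with Bonferroni. The stated window reproduces: 30 × 25 = 750 frames. An 8-minute dialogue holds 480 / 30 = 16 windows.

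**Assumed inputs (not in the article).** Independent first-order autoregressive movement with persistence near 1.0 s, a 10% difference between conditions, and 0 to 0.03 of extra dialogue-level SD.

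**Step 1: the floor with zero coupling.** Gaussian series went through the planned steps, with 1,800 dialogues per row, sampling at 5 Hz after smoothing and lags every 0.2 s to save time.

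| Persistence, partner 1 / partner 2 | Mean score | SD between dialogues |
|---|---|---|
| 1.0 / 1.0 s | 0.179 | 0.014 |
| 1.0 / 1.1 s | 0.183 | 0.015 |
| 1.1 / 1.1 s | 0.186 | 0.016 |
| 1.0 / 1.5 s | 0.192 | 0.016 |
| 1.5 / 1.5 s | 0.210 | 0.019 |

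Full 25 Hz runs gave 0.177 at 1.0 s and 0.207 at 1.5 s. Non-negative, bursty series gave lower floors with the same direction: 0.140 at 1.0 s and 0.149 at 1.5 s. The signed mean stayed near 0 (largest 0.008), so the floor comes from taking absolute values.

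**Step 2: size of a 10% shift.** If both partners change, the score rises by about 0.006. If one changes, it rises by about 0.003, roughly half. For scale, raising truly shared variance from 0 to 20% at 1.0 s moved the score from 0.180 to 0.186 in one run and from 0.177 to 0.185 in another.

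**Step 3: rejection of H2 with no coupling.** With dialogue SD s, a two-dialogue mean has variance s²/2, so the within-couple difference has variance s²/2 + s²/2 = s². Stable couple effects cancel. Hence dz = shift / s, with s = √(0.015² + extra²), and the noncentrality is dz × √150. The number of tests for Bonferroni is not given, so 8 is assumed (0.05 / 8 = 0.00625).

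| Shift | Extra SD | s | dz | Noncentrality | Rejection at 0.05 | At 0.00625 |
|---|---|---|---|---|---|---|
| 0.006 | 0 | 0.0150 | 0.400 | 4.90 | >99% | 98% |
| 0.006 | 0.02 | 0.0250 | 0.240 | 2.94 | 83% | 57% |
| 0.006 | 0.03 | 0.0335 | 0.179 | 2.19 | 59% | 28% |
| 0.003 | 0 | 0.0150 | 0.200 | 2.45 | 68% | 38% |
| 0.003 | 0.02 | 0.0250 | 0.120 | 1.47 | 31% | 10% |
| 0.003 | 0.03 | 0.0335 | 0.089 | 1.10 | 19% | 5% |

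**Step 4: does the correction work?** With bursty series, zero coupling and both partners shifted, a paired test at 0.05 rejected as follows. The correction subtracts same-condition pseudo-dyad scores.

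| Persistence longer by | Uncorrected | Corrected |
|---|---|---|
| 0% | 4.7% | 3.6% |
| 10% | 88% | 4.8% |
| 20% | 100% | 8.1% |
| 50% | 100% | 5.5% |

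These rates come from 2,000 draws on finite pools of simulated dialogues, so they carry some pool error.

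**The case against.** The strongest reply is that the text does not say the absolute score enters H2. The absolute score is one value per episode. The paragraph on H1 and H2 then speaks of windowed cross-correlations forming a time series, with windows at Level 1, and does not say whether those window values are absolute. Signed values would have almost no floor. This stands, so the point is conditional on the absolute score being carried forward. The absolute score is, however, the only movement score the article defines.

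Second, the pseudo-interaction paragraph is general, and a condensed article may leave detail to its supplement. That is fair as far as it goes. But the article does spell out the models for H1 and H2, and names pseudo-dyads in the first only.

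Third, a reader might infer that co-rumination will change movement timing and that H2 is therefore almost sure to be falsely positive. The article does not support this. It gives no movement autocorrelation, it reports no effect of the instruction on movement, and only the supporter is instructed to co-ruminate. The upper rejection rates need both partners to shift and no dialogue-level variation beyond that of the simulation. Bonferroni lowers the rates without removing the bias.

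Fourth, stable couple differences cancel in H2 and in the condition contrast of H8a. That is right: between-couple differences in style threaten H7.1 only, and only if they go with relationship quality or coping.

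**Conclusion.** The concern holds in conditional form, with moderate confidence. The aggregated absolute score has a non-zero floor that rises with movement autocorrelation, and the z-transform does not remove it. A pseudo-dyad comparison is specified for H1 alone. If the absolute score is the outcome for H2, H7.1 and H8a, those analyses cannot separate coupling from movement timing, and the error can run in either direction.

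The size depends on assumptions. For 10% longer persistence with no coupling, rejection of H2 at 0.05 runs from about 19% (supporter only, extra SD 0.03) to more than 99% (both partners, no extra SD). With a divisor of 8 the range is about 5% to 98%. No figure was computed for H7.1 or H8a. The result shows a risk that is cheap to remove; it does not show that the planned comparison is biased in fact.

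**What to change.** In the Phasic timescale section, state which score (absolute or signed, window or episode) enters H2. In that section and in Chronic timescale, make the outcome for H2, H7.1 and H8a the real score minus, or standardised against, pseudo-synchrony. Alternatively, test H2 as the condition × (real vs pseudo) interaction in one model. Report the uncorrected comparison as supportive.

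The surrogates should be matched on instruction and on sharer/supporter role, and each real partner's own series should enter the surrogates for that dialogue. For H7.1 there is one further detail. The one-partner rows above suggest that the floor is roughly additive, about f0 + g(partner 1) + g(partner 2). A plain average of the two partners' surrogate means then contains only half of g(partner 1) + g(partner 2). Subtracting the sum of the two surrogate means less the overall surrogate mean removes all of it.

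The cost is wording in two sections and extra computing, with no new data. The surrogate mean adds slight noise, which shrinks as more surrogates are used per dialogue.

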### Emotional sharing task

The emotional sharing task, which is modelled after Nils & Rimé (2009), involves a structured procedure to make participants share their emotions in a controlled experimental setting [13]. Participants will be having a total of four eight-minutes episodes with their partner to share the two experiences they each wrote down in the experience generation task. During each episode, one participant will act as a sharer (to discuss the problem) and the other participant will act as a supporter (to listen and respond to the sharer). The roles of sharer and supporter will be randomly alternated so that each participant will be a sharer and a supporter twice.

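### The Hypothesis 1 model has no term for people who appear in both real and pseudo-dyads, so its standard error is generally wrong, in a direction that depends on how dyads are identified

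*Protocol article*

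**What the plan says.** All of this is in the protocol article, Data analysis plan, Phasic timescale.

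- **Source of the pseudo-dyads.** The movement routine "calculates all possible motion energy interactions between couples in the dataset". Then "it dissociates the original pairings, followed by the extraction of a predefined amount of unique MEA datasets, each selected just once to avoid duplication". The number extracted is not given, and nothing says that each person is used equally often.
- **Movement model for Hypothesis 1.** A multilevel model is to "compare synchrony scores between real dyads and matched pseudo-dyads, accounting for the nested structure of time windows within dyads".
- **Cardiovascular model for Hypothesis 1.** The plan is to "generate a surrogate dataset of randomly paired pseudo-dyads, and then use multilevel modeling (MLM) to compare synchrony scores between real and pseudo-dyads". It adds: "This model will account for the nested structure of time windows within dyads and the repeated nature of physiological data".
- **Movement model for Hypothesis 2, same paragraph as Hypothesis 1.** Here "dyad ID and participant ID will be modeled as random effects". No participant term is named for Hypothesis 1.
- **Amount of data per dyad.** "Participants will be having a total of four eight-minutes episodes with their partner", with the movement series "cross-correlated in non-overlapping window segments of 30 seconds".

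**The concern.** Every member of a pseudo-dyad is also a member of a real dyad. A person who moves in a persistent, highly autocorrelated way raises the score of every pair that he or she enters, because the movement score averages absolute lagged correlations. The chance level of such a score is above zero and depends on each person's own autocorrelation. These person effects fall on both sides of the comparison. Persons are crossed over pairs, not nested in them, so grouping windows within dyads cannot represent the overlap.

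Hypothesis 1 is the confirmatory test that partners synchronise above chance. If the error term is too large, modest synchrony may be missed. If it is too small, synchrony may be declared where there is none. The wording allows models of either kind.

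**Working it through.** **1. The plan's own figure.** Sample size determination gives 128 dyads for two independent groups, d = 0.5, 80% power, two-sided 0.05. The normal formula gives 2 × (1.96 + 0.84)² / 0.5² ≈ 63 per group. The t version gives 64 per group, or 128 in total, so the figure reproduces. The article gives no standard error or variance share for Hypothesis 1.

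**2. Set-up.** Windows per dyad: 8 min / 30 s = 16, times 4 episodes = 64. Planned couples: 150. Write a pair's score as person effect 1 + person effect 2 + a pair-specific part + window noise. Let V be the between-dyad variance, s the share of V due to the two persons, and w the window variance. None of these is in the article. For illustration V = 0.25 and w = 1 (arbitrary units), so w/64 = 0.0156.

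**3. Separate IDs, each person used once on each side.** Person effects cancel from the real-minus-pseudo difference.

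- True variance = 2[V(1 - s) + w/64]/150
- Model variance = 2[V + w/64]/150
- Ratio of standard errors = sqrt{[V + w/64] / [V(1 - s) + w/64]}, close to 1/sqrt(1 - s) when w/64 is small

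| s (assumed) | 1/sqrt(1 - s) | formula with w/64 | simulation |
|---|---|---|---|
| 0.25 | 1.15 | 1.14 | 1.15 |
| 0.50 | 1.41 | 1.37 | 1.39 |
| 0.75 | 2.00 | 1.84 | 1.88 |

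**4. Separate IDs, other extractions (simulation).**

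- Random, unbalanced extraction, s from 0 to 0.9: 1.01 to 1.34 with 150 pseudo-dyads, and 1.03 to 2.00 with 1000.
- Real couples also differing in true synchrony (extra variance of half V), at s = 0.25, 0.50 and 0.75: 1.07, 1.27 and 1.51 one-to-one; 0.94, 1.03 and 1.13 with 1000 pseudo-dyads. The excess can vanish.

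**5. One ID shared by a real dyad and its matched pseudo-dyad, random intercept only.** The real-to-pseudo difference within an ID now falls into the window-level residual and is averaged over 150 × 64 = 9600 windows per side, as if it were window noise. If matched pairs share one member, that difference has variance D = 2[Vs/2 + V(1 - s)], and the residual variance is about w + (D/2)(64/127).

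- s = 0: residual 1.126; model standard error sqrt(2 × 1.126/9600) = 0.0153; true 0.0595; ratio 0.26.
- s = 0.9: residual 1.069; model 0.0149; true 0.0233; ratio 0.64 (simulation 0.65).

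With a normal test statistic, false-positive risk at nominal 5% is 2Φ(-1.96 × ratio): about 61% at 0.26 and 20% at 0.65. These ratios depend on the assumed w/V of 4.

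**6. Power under separate IDs.** With 150 against 150, the unpaired standard error in dyad SDs is sqrt(2/150) = 0.1155. If the sets really were independent, power is Φ(d/0.1155 - 1.96): 99%, 74% and 41% at d = 0.5, 0.3 and 0.2. If that standard error is 1.4 times the true one:

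- dyad-only test, Φ[(d/0.1155 - 1.96) × 1.4]: over 99%, 81% and 37%
- correct standard error, Φ(d/0.1155 × 1.4 - 1.96): over 99%, 95% and 68%
- true type I error of the dyad-only test, 2Φ(-1.96 × 1.4): 0.6%

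The article applies Bonferroni without giving a count. With an assumed 8 tests (0.00625), independent-sample power is 94%, 44% and 16%.

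**The case against.** The best defence is that the article condenses a fuller plan and that an exact model formula normally sits elsewhere. It never says that the two sets are separate samples; it calls the pseudo-dyads matched, and it follows cited recommendations that are not shown. This has force against any claim about direction. A reader might infer that real and pseudo-dyads are analysed as independent samples, so that the test must be conservative. The text does not fix ID coding, and one natural reading of matched gives the opposite error.

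A reader might also take a fixed inflation, say 1.4 to 2.1, as established. That range needs s between 1 - 1/1.4² = 0.49 and 1 - 1/2.1² = 0.77, separate IDs and balanced reuse. The article gives no s and describes extraction of an unspecified number for movement and random pairing for the heart data.

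Power is no general problem either: at the plan's d of 0.5 it stays at about 99%. Nor does Table 1 make later hypotheses conditional on Hypothesis 1, so it is not a gateway to them.

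What the defence does not remove is that the article does state an error structure for Hypothesis 1, and that structure omits the crossing of persons. The same paragraph names participant effects for Hypothesis 2, so brevity alone does not explain the gap.

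**Conclusion.** The concern holds in a conditional form: the stated structure does not cover people shared by real and pseudo pairs, so the Hypothesis 1 standard error is generally wrong.

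- **Separate IDs, balanced reuse:** too large, by about 1.15, 1.4 or 1.9 at assumed person shares of 0.25, 0.50 or 0.75. The excess is smaller under random extraction (about 1.0 to 1.3 with 150 pseudo-dyads) and may be nil if couples differ in true synchrony. The cost is power for d of about 0.3 or less.
- **Shared ID, random intercept only:** too small, at about 0.26 to 0.65 of the true value under the window noise assumed here, with a real risk of a false claim of synchrony.

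The problem is clearest for movement, where absolute lagged correlations are averaged. A signed zero-lag cardiovascular score would be little affected. The cardiovascular subsection describes a zero-lag calculation in one paragraph and time-lagged windows in the next, so exposure there depends on which score is used.

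**What to change.** In the movement subsection, and in the cardiovascular subsection where the score is absolute or lagged, replace the Hypothesis 1 error structure by one of these:

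1. Crossed random intercepts for the two persons forming each pair, plus a random intercept for the pair, with real versus pseudo as the fixed effect.
2. For each couple, the real score minus the mean score of the pseudo-dyads that contain its own members, testing the mean difference with uncertainty that respects shared members. A plain one-sample test of these differences is not enough: in the one-to-one simulation its standard error was still 1.08, 1.21 and 1.51 times the true one at s = 0.25, 0.50 and 0.75.

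In either case, use every person in the same number of pseudo-pairs, and state that number and how pairs are identified. The cost is one changed model formula and somewhat longer fitting; no new data are needed.
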